## 5.2 Outcomes Assessment Pilot

Before randomization and enrollment of participants, each clinical center completes a pilot study of procedures and activities involved in the major outcomes assessment visits (i.e., baseline, 6 month, 24 month, primary endpoint, and end of study). These assessments include (see data collection table in section 5.1):

1. the battery of questionnaires and surveys covering diet, activity, psychosocial factors, and medical history;
2. comprehensive physical examination;
3. blood and urine tests, including OGTT, HbA1c, lipids, liver function, etc.;
4. DXA;
5. PWC170.

The purpose of the pilot study is to provide information regarding:

- the logistics and environment for performing these procedures and activities,
- family and child reaction, and
- transfer of specimens and data among the clinical centers, coordinating center, central labs, and reading centers.

Children who participate in the pilot study meet the same inclusion and exclusion criteria as the study participants, but would not be eligible due to child's age (> 17 years) or duration of diabetes (> 2 years). The parents and child decide which of the five procedures and activities listed above they will agree to complete, and indicate by initialing those procedures and activities on the consent/assent forms. Each clinical center recruits enough children so that two children complete each procedure or activity. Children are paid \$25 for each of the five procedures/activities performed. Parents receive reimbursement for costs incurred to attend clinic visits, as for the full-scale trial.

## 5.3 Participant Retention Program

Retention refers to efforts to prevent participant dropout or withdrawal from the study. It is critically important to successfully engage and retain participation over the course of the trial. For purposes of sample size estimation, investigators have predicted withdrawal rates of 10% over each 6 month follow-up period. However, lower rates of attrition are desirable.

Challenges to retention include:

- *Burden* (e.g., the imposition caused by study procedures, frequent scheduling of procedures and study-related visits, the requirement for record keeping, the necessity of frequent glucose monitoring, the interference of study activities with other things the participant would like to do)
- *Logistics* (e.g., travel required for study participation, care of non-participating children while the parent is at a study visit, difficulty with dietary requirements such as limited access to fresh fruits and vegetables)

- *Environment* (e.g., lack of supportive individuals and institutions, deficits due to locale such as the lack of a grocery store or a safe place to be active)
- *Education* (e.g., low literacy, familial misinformation about diabetes, sociocultural mismatch between family and educator, language barriers)
- *Distrust* (e.g., the perception by the participant and/or family of being used as a 'guinea pig,' general suspicion of medical personnel or organizations, wariness of people of different ethnicity or race).

Specific strategies to systematically address each of these areas are developed. Activities at both the national and local level are utilized and coordinated to maximize retention and minimize attrition. For example, in response to the perception that "the study team is more interested in the study than the individual," the TODAY study maintains a database of ideas about positive approaches to participants. At the local level, study staff make a major effort to personalize the study (mailing out personal notes, birthday cards, etc). Individual sites develop strategies to enhance retention specific to locale (i.e., different strategies may be required in Oklahoma working with rural Native Americans as compared to working with urban African Americans in Philadelphia).

Attrition is monitored regularly by the coordinating center and the Recruitment and Retention Committee. An attempt is made to collect data on the reason for leaving the study in the case of a participant who withdraws. Assistance is offered to any site with a higher than average attrition rate. Sites are also encouraged to share their ideas and experiences via regular communication and conference calls for project and recruitment coordinators.

#### 5.4 Confidentiality

The study complies with HIPAA guidelines regarding confidentiality of patient data.

Patients who participate in the 1-6 month run-in period are assigned a study identification number:

- the first three digits indicate the clinical center and
- the next four digits are individually assigned by patient at each clinical center (0001-9999).

In addition, each patient randomized is associated with an acrostic or 'handle' of up to 6 alpha-numeric characters that is selected by the clinical center coordinator according to the following guidelines:

- neutral, i.e., not offensive, and
  - unrelated to personal characteristics or identifiers, e.g., no initials or nicknames.
- The purpose of the acrostic is two-fold. First, it acts as a check and back-up of the study ID number in case of transcription or entry error. Second, it facilitates coordinator recall of a specific patient.

All data are labeled with the study ID, including forms and specimens. All data transferred to the CoC for accumulation in the central database identify the patient only with the study ID and acrostic. The CoC does not receive any personal identifiers.

Each clinical center maintains a file on each patient that includes personal identifiers, linking name and contact information to the study ID. These data are not entered into the study data management system or into any file on the study-dedicated computer supplied by the CoC. Patient files are kept in secure locations and the clinical center is responsible for

taking every other reasonable measure (those set by the state, the site, and the study) to ensure and maintain record confidentiality and patient privacy.

Training sessions cover confidentiality principles and procedures.

## 6 Safety and Monitoring

### 6.1 Data Safety Monitoring Board (DSMB)

A Data Safety Monitoring Board consisting of appropriately qualified independent experts is appointed to provide review of data on patient safety. The purpose of the board is to assure independent review as to whether study patients are exposed to unreasonable risk because of study participation, and to monitor study progress and integrity. Board members are chosen by NIDDK in consultation with the study investigators, and a report format and reporting frequency are developed before the start of data collection. The study chair and the CoC provide periodic reports on adverse events to the committee, including summary tabulations and narrative summaries on individual events. The contents of reports are determined by the DSMB in its initial deliberations, including whether and when to perform interim efficacy analyses.

The purpose of safety reports is to present the Data Safety Monitoring Board with information regarding adverse events experienced by study patients as a result of undergoing the study procedures. Clinical centers report adverse events to the CoC in a timely fashion, including a narrative summary of the event as well as indication of the duration, perceived relationship to the study procedures, and resolution. The CoC summarizes and reports adverse events to the Data Safety Monitoring Board on a semi-annual basis unless severe or unexpected adverse events occur. These are reported promptly to the DSMB.

Following each DSMB meeting a summary of adverse events and DSMB recommendations is provided to the IRB of each participating clinical center and other institutional monitoring committees/boards as needed.

### 6.2 Safety Monitoring and Risk Management

If study medications are permanently discontinued for safety reasons, insulin therapy is not initiated unless the participant meets criteria for treatment failure or metabolic decompensation (see definition in section 4.7).

#### 6.2.1 Depression

The child, biological parent, and designated family support person complete standard depression inventories. If severe depression and/or suicidal ideation are detected either from the standard surveys or through interpersonal contact between participant and study staff, the participant is referred for care outside the study.

#### 6.2.2 Laboratory Monitoring

The purpose of periodic laboratory monitoring is to identify changes in health status that increase the risks associated with study medication (metformin and/or TZD), and to identify changes in health status as a result of participation in the trial.

After randomization, all study participants have blood glucose, SGPT/ALT, and SGOT/AST determined at every visit (every two months for the first year followed by every three months thereafter). Calculated creatinine clearance is determined at baseline and

annually. Urine ketones are measured if BG > 300 mg/dL at any clinic visit. Hemoglobin and hematocrit are measured at baseline, 2 and 6 months, and annually.

### 6.2.3 Potential Risks

Known adverse effects associated with metformin are primarily gastrointestinal (diarrhea, nausea, vomiting, abdominal bloating, flatulence, anorexia), hematologic (reduced vitamin B12 levels and, rarely, megaloblastic anemia), and the rare possibility of lactic acidosis. The risk of lactic acidosis associated with metformin use can be minimized by (1) monitoring liver transaminases, (2) monitoring renal function, and (3) temporary discontinuation of metformin before radiologic studies involving the injection of contrast dye, surgical procedures requiring reduced fluid intake, and serious illness that might be associated with hypoxia, dehydration, or shock.

Known adverse effects associated with rosiglitazone are primarily hematologic (decline in hemoglobin and hematocrit) and fluid retention and edema. Although hepatic toxicity has been observed with troglitazone (Rezulin®), which is no longer commercially available for human use, similar toxicity has not been observed so far with the other TZDs (rosiglitazone or pioglitazone). However, regular monitoring of transaminases is performed.

Potential risks of the lifestyle intervention are minor and include temporary muscle soreness and injuries associated with physical activity and slight hunger when dieting.

### 6.2.4 Procedures to Minimize Risks

- *Anemia* may be an adverse effect of either metformin or rosiglitazone. Anemia is defined as a hematocrit < 30.0%, a hemoglobin < 10 gm/dL, a decline in hematocrit by 4% from study entry, or a decline in hemoglobin by 2 gm/dL from study entry. If anemia is detected, a CBC with differential is obtained within one month. If anemia is confirmed, determination of a vitamin B12 level, examination of the blood smear, and other tests (as indicated) are performed at the discretion of the primary or study physician to help determine the etiology. Vitamin B12 and/or iron supplementation can be administered as clinically indicated. If anemia persists for more than six months despite appropriate therapy, consideration is given to discontinuing study medication.
- *Renal insufficiency* increases the risk of lactic acidosis associated with metformin. Serum creatinine is determined at baseline and annually. Using the serum creatinine, a creatinine clearance is calculated. If the calculated creatinine clearance is < 70 mL/min, study medication is discontinued for two weeks and the calculated creatinine clearance is repeated. If necessary, insulin may be temporarily used during this time. If the repeat calculated creatinine clearance is normal ( $\geq 70$  mL/min), study medication is resumed at the previous dose. If the repeat calculated creatinine clearance is again abnormal (< 70 mL/min), or if once study medication is resumed the creatinine clearance again falls to < 70 mL/min, study medication is permanently discontinued.
- *Liver complications* increase the risk of metformin-associated lactic acidosis, and drugs of the thiazolidinedione class (but not rosiglitazone or pioglitazone) have been associated with such complications. Study participants are monitored with an SGPT/ALT and an SGOT/AST every two months for the first year and every three months thereafter.

- A. If either ALT or AST level rises to 1.5-2.5 times the ULN after having been <1.5 times the ULN at baseline:
  1. Study medication is continued.
  2. Repeat ALT and AST are obtained within two weeks and blood is obtained for possible hepatitis titers that will be run if levels are still elevated. Also, if the levels remain elevated after two weeks, an evaluation must be done (minimum evaluation includes ceruloplasmin level, alpha-1 antitrypsin phenotype, ANA, anti-smooth muscle antibody, anti-LKM antibody, anti-HCV, and anti-HBc total antibody not IgM, iron, and TIBC) to rule out other liver disease (other than NAFLD). If previous evaluation had been done and was normal, then the ceruloplasmin level, Iron, TIBC, and alpha-1-antitrypsin phenotype need not be repeated. All evaluations performed because of elevated ALT and/or AST should be reviewed locally by the PI and also sent to the Safety & Monitoring Committee (SMC) for their review and consultation with a panel of GI consultants, as needed.
  3. If the ALT and AST repeated at two weeks return to < 1.5 times the ULN, resume study medication and transaminase monitoring every 2 months in follow-up year 1 and every 3 months thereafter.
  4. If ALT or AST are still 1.5-2.5 times the ULN after two weeks, hepatitis titers are negative and if all causes for transaminase elevation (other than NAFLD) are ruled out and it is presumed that the elevation is due only to non-alcoholic fatty liver disease (NAFLD), study medication is continued.
  5. While on study medication, ALT and AST should be repeated monthly for 6 months to make sure the levels are not rising. If ALT and AST decrease (to < 1.5 times the ULN) or remain stable (still 1.5-2.5 times the ULN) at 6 months, routine monitoring resumes as dictated by the protocol (every 2 months in follow-up year 1 and every 3 months thereafter).
  6. If either AST or ALT rises to > 2.5 times the ULN, then the procedures listed below in B.1-B.9 are followed.
  
- B. If either ALT or AST or both are > 2.5 times the ULN:
  1. Study medication is stopped immediately.
  2. Repeat ALT and AST in two weeks; blood is obtained for potential hepatitis titers that will be run if levels are still elevated.
  3. If levels remain elevated (ALT and/or AST >1.5 times the ULN) after two weeks, the patient must be appropriately evaluated (see A.2 above) for liver disease other than NAFLD.
  4. If the ALT and AST repeated at two weeks return to < 1.5 times the ULN, resume study medication and transaminase monitoring every 2 months in follow-up year 1 and every 3 months thereafter.
  5. If the ALT and AST repeated at two weeks decrease to 1.5-2.5 times the ULN, resume study medication and continue monitoring as in A.5 above.
  6. If the ALT or AST repeated at two weeks is > 2.5 times the ULN, the subject should remain off study medication (metformin and/or rosiglitazone) for as long as ALT and/or AST are > 2.5 times ULN. Monitoring should occur as clinically indicated, but not less frequently than every 2 months in follow-up year 1 and every 3 months thereafter.
  7. If AST and ALT subsequently return to <2.5 times the ULN and the transaminase elevation was identified as due to a specific transient and reversible etiology, study medication can be resumed.

8. If AST and ALT return to < 2.5 times ULN and no specific transient and reversible cause for the elevation was identified, rosiglitazone should be permanently discontinued, but metformin should be resumed. Monitoring should be performed as in A.5 above.
9. After a second episode of AST and/or ALT rising to > 2.5 times ULN without a specific transient and reversible cause being identified, both rosiglitazone and metformin are permanently discontinued. Continued monitoring should be performed as clinically indicated.

Participants and their families are instructed that in the event they develop malaise, vomiting, dark urine, jaundice, or right upper quadrant abdominal discomfort, they should stop study medication and contact the study clinical center immediately. Upon notification, the center staff must obtain blood for ALT and AST as soon as possible and within one week. Based on these results, the algorithm described above is followed.

- *Gastrointestinal (GI) symptoms* are a common occurrence with metformin. However, these symptoms more commonly occur early in the course of treatment. Since all eligible participants are placed on the maximal tolerated metformin dose (between 500 mg bid and 1000 mg bid) during the run-in period, few additional gastrointestinal side effects are anticipated in these patients. If GI side effects develop and are mild, the patient is encouraged to remain on the study medication. If GI side effects are moderate or difficult to tolerate, metformin (but not rosiglitazone) is reduced to the next lowest dose (for example, 1000 mg bid to 1000 mg + 500 mg; 1000 mg + 500 mg to 500 mg bid; etc.). If symptoms persist, metformin is reduced to the next step. If GI symptoms resolve, metformin is re-escalated by 500 mg per day each week until reaching the previously tolerated dose. If symptoms persist on a dose of metformin that is only 500 mg bid, study medication is discontinued.
- *Edema* is considered clinically significant if there is pitting edema above the patient's ankle. A thorough evaluation of potential causes is conducted, and the dose of study medication is reduced (if necessary, medication is stopped). As with any serious adverse event, if the patient is experiencing severe symptoms along with clinically significant edema, the SAE should be reported according to study procedures.
- *Severe hypoglycemia* is defined by the need to be treated with glucagon, the need for a third party to resolve a hypoglycemic episode, or loss of consciousness or seizure. Study medications are adjusted downward. If after one month there are no additional hypoglycemic events and if HbA1c values rise > 6%, then the dose of study medications is returned to the previous dose. In case of a second episode of severe hypoglycemia, the dose is decreased until the end of the trial. If more than two severe hypoglycemic events occur in the same patient in the absence of insulin, then the patient is unmasked and study medications are adjusted downward until hypoglycemia is resolved.  
If severe hypoglycemia occurs while on insulin, the insulin dose is reduced by 20%. After one month, if there are not additional hypoglycemic events or if HbA1c values rise to > 6%, then the dose is increased by 10% a month until it returns to the previous level. If a second episode of severe hypoglycemia occurs, insulin dosage adjustment is performed at the discretion of the investigator.
- *Study medication* is temporarily discontinued 24 hours before, during, and for 48 hours after any of the following events: 1) procedure involving the injection of contrast dye; 2)

surgery or other procedure requiring general anesthesia; 3) any illness that could be associated with hypoxia, circulatory failure, or dehydration; 4) hospitalization. Serum creatinine should be rechecked and creatinine clearance calculated as soon as feasible (but no sooner than 48 hours after the conclusion of the event) and study medication can be restarted if the calculated creatinine clearance is  $\geq 70$  mL/min. If values remain  $< 70$  mL/min, a creatinine clearance is repeated at 2, 4, 8, and 12 weeks. Study medication is restarted when the creatinine clearance is  $\geq 70$  mL/min. If creatinine clearance remains  $< 70$  mL/min at 12 weeks, then study medication is permanently discontinued.

- Other indications for temporary or permanent discontinuation of study medication include:
  - *Pregnancy*: No study medication should be administered for the duration of pregnancy and insulin should be instituted.
  - *Lactation*: No study medication should be administered to women who are nursing a baby.
  - *Lactic acidosis*: Any study patient who experiences a bout of lactic acidosis has study medication permanently discontinued.
  - *DKA*: Any study patient who experiences an episode of DKA follows the safety procedures for a participant who has experienced metabolic decompensation.
  - *Dermatological problems*: Any study patient who experiences severe dermatological problems, such as urticaria, bullous rashes, exfoliative dermatitis, Stevens-Johnson syndrome, thought to be related to study medication has study medication permanently discontinued.

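### Section 6.2.4 gives opposite instructions for a second, unexplained transaminase rise above 2.5 x ULN that has fallen by the two-week repeat

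*Protocol*

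**What the plan says.** Protocol section 6.2.4, Liver complications, part B covers any ALT or AST above 2.5 x ULN. Step A.6 also sends patients there from the milder branch, where "the procedures listed below in B.1-B.9 are followed". No step before B.9 mentions episode number.

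- **B.1:** "Study medication is stopped immediately".
- **B.2:** ALT and AST are repeated at two weeks. Blood is kept for hepatitis titers, which are run only if levels are still raised.
- **B.3:** "If levels remain elevated (ALT and/or AST >1.5 times the ULN) after two weeks, the patient must be appropriately evaluated" for liver disease other than NAFLD.
- **B.4:** "If the ALT and AST repeated at two weeks return to < 1.5 times the ULN, resume study medication".
- **B.5:** if the two-week values "decrease to 1.5-2.5 times the ULN, resume study medication and continue monitoring as in A.5 above".
- **B.6:** if the two-week value is still above 2.5 x ULN, medication stays off while that lasts.
- **B.7:** if values later fall below 2.5 x ULN and a transient, reversible cause was found, medication can be resumed. The word *subsequently* ties this step to B.6.
- **B.8:** if values fall below 2.5 x ULN and no such cause was found, rosiglitazone is withdrawn permanently and metformin resumed. The word *subsequently* does not appear.
- **B.9:** "After a second episode of AST and/or ALT rising to > 2.5 times ULN without a specific transient and reversible cause being identified", both drugs are withdrawn permanently.

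**The concern.** B.4 and B.5 are decided by the two-week level alone. B.9 is decided by episode number and cause alone. Nothing prevents one patient from satisfying both sets of conditions, and the actions are opposite: re-exposure, or permanent loss of both drugs, on identical facts.

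The outcome may then depend on which line a site reads. Metformin is given in all three arms, so a permanent stop under B.9 can reach a patient in any of them. Section 6.2 raises the stakes: after a permanent stop for safety, insulin is not started unless the criteria for treatment failure or metabolic decompensation are met. Section 8.2 keeps the patient in the randomized arm for analysis. The reading chosen thus decides whether a participant goes on without glucose-lowering study drug while still counting toward the primary comparison.

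**Working it through.** The protocol states no figure that can be recomputed here. The check is a decision table: episode (first, second) x two-week repeat (< 1.5, 1.5-2.5, > 2.5 x ULN) x cause identified (yes, no), which gives 2 x 3 x 2 = 12 combinations. For each, every step whose written condition is met was listed. For a second episode I take both episodes as unexplained, so that B.9 is met however its wording is parsed.

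**Cause identified (6 combinations).** B.8 and B.9 are not triggered. B.4, B.5 or B.6 followed by B.7 apply without contradiction.

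**No cause identified (6 combinations):**

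| Episode | Two-week repeat | Steps met | Result |
|---|---|---|---|
| First | < 1.5 | B.4: resume. B.8 read literally: rosiglitazone stopped for good | Scope of B.8 unclear |
| First | 1.5-2.5 | B.5: resume. B.8 read literally: rosiglitazone stopped for good | Scope of B.8 unclear |
| First | > 2.5 | B.6: stay off, then B.8 after a later fall | Consistent |
| Second | < 1.5 | B.4: resume. B.9: both drugs stopped for good | Direct conflict |
| Second | 1.5-2.5 | B.5: resume. B.9: both drugs stopped for good | Direct conflict |
| Second | > 2.5 | B.6: stay off. After a later fall, B.8 and B.9 overlap | B.9 reads naturally as the escalation of B.8 |

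The tally is 2 direct conflicts, 2 unclear overlaps, 1 benign overlap and 1 clean path among the six unexplained combinations, and none among the six explained ones.

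**Work-up.** B.9 needs to know whether a cause was identified. The protocol requires the following on the two conflicting paths:

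- Repeat < 1.5 x ULN (B.4 path): B.3 is not triggered because its threshold is above 1.5 x ULN. The B.2 titers are not triggered because levels are no longer raised. Unless a cause happens to be apparent, B.9's condition is met by default.
- Repeat above 1.5 and up to 2.5 x ULN (B.5 path): B.3 does require an evaluation. Only the resume-or-stop conflict applies.

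**The two candidate rules of precedence.** If B.9 overrides B.4 and B.5, the conflict goes, but the B.4 path still ends in a permanent stop that depends on a cause for which no search is required. If B.7-B.9 apply only after B.6, the conflict also goes, but repeated unexplained rises that settle by week two never reach B.9. The two rules lead to different handling, and the text states neither.

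**The case against.** The best defence is that an ordinary reading removes the clash. B.6 to B.9 can be taken as one sequence: B.7 to B.9 share the same cause criterion, B.9 steps up from B.8, and B.4 and B.5 are separate exits at week two. Alternatively, B.9 is the only step that addresses a second episode, and a specific rule governs a general one. Both readings are reasonable. They give different instructions, however, and B.9 is triggered by the rise itself, not by persistence at two weeks. Section 1 refers to a manual of procedures with more detail. It is not at hand and might settle the matter, but the protocol should not contradict itself.

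Three stronger claims are tempting, and the document does not support them.

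- *Monitoring is inverted.* A reader might set A.5 ("ALT and AST should be repeated monthly for 6 months") against B.6 ("not less frequently than every 2 months in follow-up year 1 and every 3 months thereafter") and infer that sicker patients are tested less often. A.5 applies to patients taking study medication and B.6 to patients off it. The B.6 interval is only a floor beneath testing as clinically indicated. There is no contradiction.
- *B.5 and B.8 must give the same result for the same level.* B.5 deals with a fall within two weeks and B.8 reads naturally as dealing with a later one. Treating early and late resolution differently is a legitimate clinical choice. What remains is B.8's missing *subsequently*, which leaves its scope in a first episode unclear.
- *No cause is ever sought on the B.4 path.* B.3 sets when evaluation is mandatory. It does not stop an investigator from recognizing a cause such as intercurrent illness. The accurate statement is that no work-up is required.

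The defence is also right about frequency. Sections 3.2.3 and 3.2.4 admit patients at 1.5-2.5 x ULN with presumed NAFLD, so crossings of 2.5 x ULN are foreseeable. Those who return to their entry range fall under B.5, where an evaluation above 1.5 x ULN is required. They are no evidence for the frequency of the B.4 path.

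**Conclusion.** The point holds in a limited form. For a second rise above 2.5 x ULN with no transient, reversible cause identified, the protocol tells sites both to resume study medication (B.4 or B.5) and to withdraw both drugs permanently (B.9), and gives no order of precedence. That is 2 of 12 combinations in direct conflict. On one of the two, the B.4 path, the deciding condition rests on an identification for which the protocol requires no work-up. A further 2 combinations, in a first episode, are unclear because of B.8's wording.

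The conclusion assumes that no cause was identified and that the manual of procedures does not settle precedence. The number of patients affected cannot be estimated, because the protocol gives no event rate. Opposite safety instructions on the same facts should be corrected even if the path is rare. This review takes no view on which instruction is right.

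**What to change.** Reconcile section 6.2.4, B.2 to B.9, in two places:

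1. State which of B.4, B.5, B.8 and B.9 governs when levels have fallen by week two, separately for a first and a second episode. This includes saying whether B.8 and B.9 apply only to patients who passed through B.6.
2. Reconcile B.9's dependence on an identified cause with the conditions in B.2 and B.3 that decide when a work-up is required, so that the text says how cause status is established on the B.4 path.

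The Safety and Monitoring Committee should decide the clinical content of both. The cost is amendment wording, with the committee vote and IRB resubmission that section 9.8 requires. Sample size, the analysis and the visit schedule need no change for this.
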